### Sample size calculation

2.6

This is a signal-seeking Early Phase 2 study to inform sample size calculation for a larger Phase 2 study after completion. Power calculation based on incidence of response: Assuming ORR is <1% in untreated immunotherapy-resistant melanoma, using Simon 2-stage design, initial recruitment (n = 17) is 80% powered to detect ORR of 20% (α = 0.05). The second stage will be initiated if there is at least one response in the first 17 patients. In the second stage, 23 additional patients (n = 40) will be enrolled to achieve 80% power to detect 10% ORR (α = 0.05).

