#### Secondary outcome objectives

2.1.2

1.Quantify response rate (RR) to administration of 2 cycles of decitabine and carboplatin/28 day cycle using RECIST criteria. This data will be used to calculate sample size and determine statistical analysis plan for larger Phase II study.

This is a single-center study conducted at Calvary Mater Hospital, Newcastle NSW Australia in a single group of 30 patients. Surgical biopsies will be conducted as day surgery and all participants will receive treatment as day oncology patients. There will be no requirement for participants to be admitted to hospital.

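### The 80% power and alpha of 0.05 claimed for the first 17 patients do not belong to the only stage-1 rule given, and no cut-off at 17 gives 80% power

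*Protocol article*

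**What the plan says.** All of the design figures are in section 2.6 (Sample size calculation) of the protocol article.

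- Null: "Assuming ORR is <1% in untreated immunotherapy-resistant melanoma".
- Method: "using Simon 2-stage design".
- Stage 1: "initial recruitment (n = 17) is 80% powered to detect ORR of 20% (α = 0.05").
- Gate: "The second stage will be initiated if there is at least one response in the first 17 patients".
- Stage 2: "23 additional patients (n = 40) will be enrolled to achieve 80% power to detect 10% ORR (α = 0.05").

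The section gives no number of responses at which activity would be declared, at 17 or at 40. Section 2.7 (Data analysis plan) does not give one either. Section 2.1.2 says that the study is run "in a single group of 30 patients", and the abstract and article summary also give 30.

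**The concern.** A Simon two-stage design has one null rate, one alternative, and one alpha and power for the whole procedure. Its first stage usually serves only to stop early for lack of activity. Section 2.6 instead gives each stage its own target, power and alpha: 20% at 17 patients and 10% at 40. A reader who wants to know which rule has 80% power and alpha 0.05 at 17 patients finds only one threshold, the condition for opening stage 2.

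This is the only power calculation in the article, and sections 2.1.2 and 2.3.1 say that the response data will be used to size the larger Phase 2 study. With a power and an alpha printed for stage 1 and a single threshold beside them, one response in 17 could be reported as a signal at the 0.05 level. The design does not support that claim.

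**Working it through.** **Inputs.** From section 2.6: null rate p0 below 1% (computed at 1%, with lower values shown), n1 = 17, n = 17 + 23 = 40, alternatives 20% and 10%, alpha 0.05. The sidedness of alpha is not stated. A rule of the form r or more responses is one-sided by construction. All figures are exact binomial.

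**Step 1. The 17-patient claim (80% at 20%, alpha 0.05).** For X responses among 17, P(X = 0) = (1 − p)^17 and P(X = 1) = 17p(1 − p)^16.

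- At p = 0.01: P(X = 0) = 0.99^17 = 0.843 and P(X = 1) = 0.145.
- At p = 0.20: P(X = 0) = 0.8^17 = 0.0225 and P(X = 1) = 0.0957.

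| Cut-off at 17 | Probability at 1% | Probability at 20% |
|---|---|---|
| 1 or more | 15.7% | 97.7% |
| 2 or more | 1.2% | 88.2% |
| 3 or more | 0.06% | 69.0% |

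The stated 80% is not reproduced by any cut-off. If 2 or more were intended, 14 patients would be enough: 1 − 0.8^14 − 14 × 0.2 × 0.8^13 = 0.802, with alpha 0.008. So 17 does not follow from a 20% target with 80% power.

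**Step 2. Dependence on the null.** The chance of passing the gate under the null is 1 − (1 − p0)^17: 15.7% at p0 = 1%, 8.2% at 0.5%, 5.0% at 0.3% and 1.7% at 0.1%. The 97.7% at a true rate of 20% does not depend on p0.

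**Step 3. The 40-patient claim (80% at 10%, alpha 0.05).** Suppose the gate is followed by success at 2 or more of 40. A trial that passes the gate then fails only with exactly one response in stage 1 and none among the next 23:

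P(success) = P(X ≥ 1) − P(X = 1) × (1 − p)^23.

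- At p = 0.01: 0.1571 − 0.1447 × 0.7936 = 0.042.
- At p = 0.10: 0.8332 − 0.3150 × 0.0886 = 0.805.

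This reproduces the plan's figure. Of the final cut-offs from 1 to 4, only 2 meets both stated values: 1 or more gives alpha 15.7% and power 83.3%, 3 or more gives 0.6% and 70.9%, and 4 or more gives 0.06% and 54.5%.

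**Step 4. Where the 17 comes from.** A search over two-stage designs for 1% against 10%, with alpha at most 0.05 and power at least 80%, gives as the optimal design n1 = 17, n = 39, continue on 1 or more, success on 2 or more (alpha 0.041, power 0.802). The stage-1 size and gate therefore fit the 10% target. The 20% target has no place in that design.

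**Step 5. If enrolment ends at 30.** The formula in step 3 with 13 further patients gives 0.1571 − 0.1447 × 0.8775 = 0.030 at 1%, and 0.8332 − 0.3150 × 0.2542 = 0.753 at 10%.

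**The case against.** A reader might infer that the design has a type I error of 16%. The article does not support this. It uses one response in 17 only to decide whether stage 2 opens, and never calls it a positive result. The 15.7% is the chance of continuing under the null, and with 2 or more of 40 as the final rule the design's type I error is 4.2%. The 15.7% is also an upper limit, because the assumed null is below 1%. This objection stands in full.

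A second objection is that power is normally quoted as a minimum and alpha as a maximum. On that reading 2 or more of 17 satisfies the sentence, with 88.2% power at alpha 1.2%. This stands in part: the sentence is not false under every rule. But that rule is not given, and the threshold that is given does not fit.

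A third objection is that the final cut-off can be recovered from the stated figures, and that a condensed article may leave it to the full protocol. This also stands. The missing cut-off at 40 is not a fault by itself, and the 40-patient power statement is correct under 2 or more. Condensation does not explain the 17-patient sentence, however, because that sentence is printed and does not match the rule printed after it.

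**Conclusion.** The point holds in a limited form. Section 2.6 credits the first 17 patients with 80% power at a 20% response rate and alpha 0.05. The only stage-1 rule it states is passed with probability 97.7% at 20% and 15.7% at a null of 1%. No cut-off at 17 gives 80%, and 2 or more meets the figures only as bounds.

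The 15.7% rests on p0 = 1%, and the gate's null probability is at or below 5% once p0 is about 0.3% or lower. The mismatch with 80% power remains at any null. The 15.7% would be a type I error only if one response in 17 were taken as success, which the article does not say. The design for 10% at 40 patients is sound with a final rule of 2 or more.

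The sentence should be corrected, but it is not critical. Response rate is a secondary outcome, and the primary methylation, XPC and immune-marker comparisons do not depend on it.

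**What to change.** Delete the 20% sentence, or restate it with its own cut-off and exact figures. Then give one design in the sponsor's own numbers, for example:

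*Null response rate 1%, alternative 10%. Stage 1: 17 patients; stop if there are no responses (probability 84% under the null, 17% under the alternative). No claim of activity is made at stage 1. Stage 2: 23 further patients, 40 in all; activity is declared with 2 or more responses. One-sided alpha 0.042, power 0.805.*

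Reconcile the total in the same edit. Section 2.6 gives 40, while the abstract, article summary and section 2.1.2 give 30. If enrolment is to stop at 30, the figures for 2 or more of 30 are alpha 0.030 and power 0.753 at a 10% response rate, and the 80% claim must be withdrawn.

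The cost is one paragraph and a consistent total. No patients are needed beyond the 40 already in section 2.6. If the trial had been resourced for 30, the choice is between 10 more patients and the lower stated power.

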**Methods and analysis::**

This single-site early phase 2 clinical trial will be conducted in 30 patients with metastatic melanoma that are resistant to all approved therapies. Patients will receive 2 × 4-week cycles of decitabine 7 mg/m^2^ IVI/day for 5 days (D1-D5) followed by Carboplatin AUC 5 IVI on D8; Week 3 and Week 4 no treatment. The primary objective is to determine DNA methylation and DNA repair levels before, and immediately after treatment; quantify immune-response markers (PDL-1, PD-1, CD4/CD8, and CD68) in blood, tumor and microenvironment before treatment and after 2 cycles. The secondary outcome objective is to quantify response rate (RR) to administration of 2 cycles of decitabine and carboplatin cycle using response evaluation criteria in solid tumors (RECIST 1.1) criteria. This data will be used to calculate sample size and determine statistical analysis plan for larger Phase 2 study.

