**Trial registration details::**

Australian New Zealand Clinical Trial Registry ACTRN12616000440426

Article summaryThis is a new combination of drugs for the treatment of metastatic melanoma to determine if the tumor becomes immunogenic in order for it to be used as a priming regime in combination with immunotherapy in future.Early phase II, open label single cohort study of 30 patients at single site (Calvary Mater Hospital Newcastle, Australia)This early phase II study will assess the feasibility of a larger Phase II study and determine outcome measures required to calculate sample sizes and develop a statistical plan.

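### Enrolment is given as 30 patients in three places, but the two-stage design in section 2.6 can end only at 17 or 40; the size and the power statement must be reconciled

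*Protocol article*

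**What the plan says.** Three places give a fixed size of 30:

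- Abstract, Methods and analysis: "This single-site early phase 2 clinical trial will be conducted in 30 patients with metastatic melanoma".
- Article summary: "open label single cohort study of 30 patients at single site".
- Section 2.1.2, in the paragraph on setting: "in a single group of 30 patients".

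Section 2.6 gives the only sample-size calculation. It names a Simon two-stage design and sets the null as follows: "Assuming ORR is <1% in untreated immunotherapy-resistant melanoma". The first stage has 17 patients and is described as having 80% power for a response rate of 20% at α = 0.05. The continuation rule is: "The second stage will be initiated if there is at least one response in the first 17 patients". The second stage is: "In the second stage, 23 additional patients (n = 40) will be enrolled to achieve 80% power to detect 10% ORR", again at α = 0.05.

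Section 2.6 does not say how many responses among 40 would count as success, or whether α is one-sided. It does not mention 30.

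**The concern.** Under section 2.6 the trial stops at 17 if nobody responds and otherwise goes on to 17 + 23 = 40. Thirty is neither end point. A reader of the abstract or section 2.1.2 would close enrolment at 30; a reader of section 2.6 would close it at 17 or 40. The maximum number of patients is a basic parameter of the trial, and here it depends on which section is read.

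The power statement is tied to the same number. If enrolment closes at 30 after the 17-patient gate has been passed, the second stage ends after 13 of its 23 patients, and the 80% claimed for 40 cannot be carried over without checking. That claim belongs to the response rate, the only endpoint for which the article gives any power justification and the one meant to inform the size of the larger Phase II trial.

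**Working it through.** **Inputs.** From section 2.6: first stage n1 = 17, continue if X1 ≥ 1, second stage n2 = 23, α = 0.05, alternative response rate 10%. Assumed: null rate p0 = 1% exactly (the article says below 1%), one-sided α, and success at 2 or more responses overall.

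**Why 2 or more.** At N = 40 and p0 = 1%, with the gate in place:

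- success at ≥1: type I error 15.7%, too high;
- success at ≥2: type I error 4.2%, power 80.5%;
- success at ≥3: power 70.9%, too low.

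Only ≥2 fits both stated targets.

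**Formula.** With gate ≥1 and success ≥2,

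P(success) = P(X1 ≥ 2) + P(X1 = 1) × [1 − (1 − p)^n2].

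**Reproducing the stated figure, N = 40 (n2 = 23).**

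- p = 0.10: P(X1 ≥ 1) = 0.8332 and P(X1 ≥ 2) = 0.5182, so P(X1 = 1) = 0.3150. Power = 0.5182 + 0.3150 × (1 − 0.9^23) = 0.5182 + 0.3150 × 0.9114 = 0.805.
- p = 0.01: P(X1 ≥ 1) = 0.1571 and P(X1 ≥ 2) = 0.0123, so P(X1 = 1) = 0.1447. Type I error = 0.0123 + 0.1447 × (1 − 0.99^23) = 0.0123 + 0.1447 × 0.2064 = 0.042.

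The stated 80% at α = 0.05 reproduces, so 40 is what the calculation supports and is not a slip for 30.

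**Same gate, enrolment closed at 30 (n2 = 13).**

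- p = 0.10: 0.5182 + 0.3150 × (1 − 0.9^13) = 0.5182 + 0.3150 × 0.7458 = 0.753.
- p = 0.01: 0.0123 + 0.1447 × (1 − 0.99^13) = 0.0123 + 0.1447 × 0.1225 = 0.030.
- Power reaches 80% at a response rate of 11.0%.

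**Thirty patients under other designs, success ≥2, response rate 10%.**

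- Single stage: 1 − 0.9^30 − 30 × 0.1 × 0.9^29 = 0.816; type I error 3.6%.
- Gate of ≥1 response placed at 23 patients: 0.803.

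| Design (success ≥2) | Type I error at 1% | Power at 10% |
|---|---|---|
| 17 + 23 = 40 | 4.2% | 80.5% |
| 17 + 13 = 30 | 3.0% | 75.3% |
| Single stage, 30 | 3.6% | 81.6% |

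With the gate at 17 and success at ≥2, power is 79.9% at N = 38 and 80.2% at N = 39, so 40 is not the only size that reaches 80%.

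**Sensitivity to p0.** A smaller null lowers type I error (0.8% at p0 = 0.5%, N = 30) and leaves the 75.3% unchanged. Success at ≥1 would keep α within 0.05 only if 1 − (1 − p0)^17 ≤ 0.05, that is p0 ≤ 0.3%. Passing the gate would then already be success and the second stage could not change the result, so this is unlikely to be the intended rule.

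**The case against.** A reader might infer that 30 patients cannot give 80% power for a 10% response rate. The documents do not support that. The shortfall comes from combining 30 with a look at 17; a single-stage test of 30, or a later look, reaches 80%. What stands is that these are different designs from the one in section 2.6.

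A reader might also infer that closing at 30 undermines error control. It does not: under the assumed rule, type I error falls from 4.2% to 3.0%. Only the power moves, by about five points. The separate statement about 17 patients and a 20% response rate does not depend on whether the total is 30 or 40.

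The 75% figure rests on a final rule that is inferred. That is fair, although the inferred rule is the one that reproduces the article's own figures at p0 = 1%.

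Finally, response rate is secondary, the primary outcomes are paired biomarker comparisons to which this power does not apply, and section 2.6 describes a signal-seeking study. On that basis a fall from 80% to 75% would not by itself be serious. This is accepted. It does not remove the contradiction: the three statements of 30 describe the whole trial, and nothing presents 30 as an evaluable subset, a biomarker subset or an average.

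**Conclusion.** The contradiction holds on the face of the article: 30 in three places, against 17 or 40 in section 2.6, with no link between them. It is an inconsistency and not an arithmetic error, since section 2.6 is correct on its own terms for 40.

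The effect on power is secondary and conditional. If the 17-patient gate is kept, success means two or more responses and the null rate is 1%, closing at 30 gives about 75% power at a 10% response rate instead of 80%, with type I error 3.0%. The point needs correcting because the stated size and the stated design cannot both be carried out, not because of those five points of power.

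**What to change.** Use one enrolment number throughout, and state the final success rule and the sidedness of α in section 2.6. Which option applies depends on the intended size.

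- **If 30 is intended:** rewrite section 2.6 for 30 with its own figures. With the gate kept, for example: 17 + 13 patients, success at two or more responses, about 75% power at a 10% response rate (80% at about 11%), one-sided type I error about 0.03 at a null rate of 1%. If the gate is dropped or moved, give the figures for that design. The cost is wording and, with the gate kept, a slightly less favourable power statement.
- **If the 17/40 design is intended:** replace 30 in the abstract, article summary and section 2.1.2 with 17, or up to 40 if at least one of the first 17 responds. This means up to 40 − 30 = 10 more patients than those sections state, each with two excision biopsies under section 2.3. The article reports ethics approval of protocol version 1.1 but not the number approved, so the need for an amendment cannot be excluded.

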### Data analysis plan

2.7

All data for primary outcomes will be tested before and after treatment using paired t-test with Bonferroni correction when required.

Objective response rate (ORR) is defined as the proportion of patients with tumor size reduction of 30% after onset of treatment until documented tumor progression. ORR will be calculated using RECIST scores at weeks −1 and 9. Before-after study (paired *t* test): RECIST scores will undergo paired t-test analysis to determine statistical differences in response based on tumor size. The results of the before-after study will be used to calculate the sample size for a large multi-center Phase 2 trial.

Waterfall plot of tumor shrinkage is a data visualization technique that depicts tumor shrinkage that is the best observed % change of sum of target lesions from baseline.

Overall survival will be calculated at each RECIST data collection point (weeks −1 and 9) and every 6 months until study completion. Overall survival will be calculated as the time from initiation of the trial treatment to death from any cause. Kaplan-Meier plots for sub-groups based on primary outcome data will be generated every 6 months for the duration of the study.

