#### Primary outcome objectives

2.1.1

1.Determine DNA methylation and XPC levels before, and immediately after treatment, that is, at study entry and after 2 months.2.Quantify immune-response markers (PDL-1, PD-1, CD4/CD8, and CD68) in blood, tumor and microenvironment and immune response in blood before treatment and after 2 cycles.

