### Data collection

2.3

Before treatment (Day -14) and on Day 57 (week 9) an excision biopsy of subcutaneous metastatic lesion or lymph node and 9 mL blood collection will be collected where. Tumor biopsies will be used for analysis of DNA methylation (whole genome bisulfite sequencing and ELISA assay), XPC mRNA and protein levels. Statistically significant differences in methylation and XPC levels will be tested before and after treatment using paired *t* test with Bonferroni correction.

Tumor biopsies will also be used for immunohistochemistry to assess the immune-response markers: CD4 and CD8 inside tumor, number of tumor cells with PDL1 expression, CD8 with PDL1 expression, CD8 with CD45RO expression, CD8 with granzyme B, TIM3, perforin as described in Tumeh et al.^[9]^ Blood collected will be tested for immune activation profile and INF gamma signature. All data will be tested before and after treatment using paired t-test with Bonferroni correction.

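### The only stated link between the primary biomarkers and survival is Kaplan-Meier curves by sub-group with no cut fixed; a continuous exploratory Cox model would give an effect estimate at little cost

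*Protocol article*

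**What the plan says.** The primary objectives in section 2.1.1 concern measured levels. The first is "Determine DNA methylation and XPC levels before, and immediately after treatment, that is, at study entry and after 2 months". The second is "Quantify immune-response markers (PDL-1, PD-1, CD4/CD8, and CD68) in blood, tumor and microenvironment and immune response in blood before treatment and after 2 cycles". Section 2.3 names the assays: "Tumor biopsies will be used for analysis of DNA methylation (whole genome bisulfite sequencing and ELISA assay), XPC mRNA and protein levels". It adds counts of immune and tumor cells by immunohistochemistry, and blood profiles.

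Section 2.7 keeps these data on their measured scale for the before-after comparison: "All data for primary outcomes will be tested before and after treatment using paired t-test with Bonferroni correction when required".

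The same section defines survival: "Overall survival will be calculated as the time from initiation of the trial treatment to death from any cause". It then gives the one sentence in the article that joins the biomarkers to survival: "Kaplan-Meier plots for sub-groups based on primary outcome data will be generated every 6 months for the duration of the study". It names no cut-point, number of groups, model, test or significance level for that link. Overall survival is not among the objectives in sections 2.1.1 and 2.1.2.

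**The concern.** A Kaplan-Meier plot by sub-group needs groups, so a continuous marker has to be cut before it can be shown. Three things follow.

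- The cut discards the ordering of patients within each group. At the sample sizes in the article, a two-way split leaves about 8 to 20 patients per curve.
- The plots are repeated every 6 months and no cut is fixed. A cut could therefore be chosen, or changed, once survival has been seen, and the curves could separate because of that choice.
- The plots give no estimate, with an interval, of how the hazard changes with the size of the marker change.

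In a signal-seeking study, a real gradient between biomarker change and survival could be missed, or an apparent one could be produced by the cut.

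**Working it through.** **The plan's own figures.** The article states no power for survival by biomarker. Its only power statement, in section 2.6, concerns response rate. No final boundary is given for the 17 + 23 design. If it is taken as at least 2 responses in 40, after at least 1 in the first 17:

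- At a 10% response rate, power = 1 − [0.9^17 + 17(0.1)(0.9^16)(0.9^23)] = 1 − (0.167 + 0.028) = 80.5%.
- At 1%, the same expression gives a type I error of 0.042.

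The 80% figure for 40 patients is therefore reproduced, but it says nothing about survival.

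**Inputs from the article.** Sample size is 17 or 40 in section 2.6 and 30 in the abstract and section 2.1.2. These are not reconciled, so all three are used.

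**Inputs assumed, because the article gives none.** A normally distributed marker measured without error; a log-linear hazard; hazard ratio (HR) per standard deviation (SD) from 1.3 to 3; 60%, 80% or 100% of patients dead; a two-sided 5% test. A log-rank test on the split is also assumed, although none is planned.

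**Information kept.** A split at the median multiplies the effect by φ(0)/√(0.5 × 0.5) = 0.399/0.5 = 0.798. Squared, this is 2/π = 0.64, so 30 patients carry the information of about 30 × 0.64 = 19.

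**Power by formula.** With d deaths:

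- continuous marker: Φ(√d × ln HR − 1.96)
- median split: Φ(0.798 × √d × ln HR − 1.96)

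For d = 24 (30 patients, 80% dead) and HR 1.5, √24 × 0.4055 = 1.986. Continuous: Φ(0.026) = 51.1%. Split: Φ(1.585 − 1.96) = 35.4%. The loss is 15.7 points.

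Other losses by formula, for HR 1.5 and HR 2.0 respectively: 7.5 and 17.5 points at 10 deaths; 12.1 and 19.0 at 17; 17.7 and 10.9 at 30; 19.3 and 5.4 at 40.

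**Check by simulation** (6,000 trials per setting; log-rank on a median split against the Cox likelihood-ratio test; 80% dead). Points of power lost:

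| Patients | HR 1.3 | HR 1.5 | HR 2.0 | Stronger effect |
|---|---|---|---|---|
| 17 | 3 | 7 | 18 | 20 (HR 2.5) |
| 30 | 7 | 15 | 20 | 8 (HR 3.0) |
| 40 | 9 | 19 | 16 | 3 (HR 3.0) |

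Over the full grid of 54 settings the loss runs from 1 to 22 points, and 27 of the 54 lie strictly within 10 to 20. With HR limited to 1.5 to 2.5, 23 of 36 lie strictly within 10 to 20, and 30 of 36 within 9 to 21.5. Using the Wald test, or an upper-third split, changes these last two counts to 28 and 30 or 31.

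The loss is small at both ends: with a weak effect, power is low either way; with a strong effect and many deaths, it is near 100% either way.

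**Type I error.** In a further simulation (3,000 trials per setting), null rejection rates were 5.7% to 6.0% for the continuous test and 6.3% to 6.5% for the split. The gain is not bought with extra false positives.

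**The case against.** The strongest reply is that the article promises plots, not a test. Where a test is meant, as for the biomarkers and the RECIST scores, the paired t-test is named. The survival curves sit beside a waterfall plot, which is also a display. **This stands.** A reader might infer that the plan as written gives up 10 to 20 points of power, but the text does not support that: the loss exists only if someone compares the curves formally.

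A reader might also infer that the biomarker-survival result is meant to feed the next trial, citing section 2.1.2: "This data will be used to calculate sample size and determine statistical analysis plan for larger Phase II study". There, the data referred to are the RECIST response rates. Section 2.3.1 says the same of response, and section 2.7 of the before-after comparison. No planned use of a biomarker hazard ratio is stated.

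Nor does the text say that every biomarker will be cut, that the cut will be at the median, or that it will be made on the change. The Introduction classes methylation of a region upstream of XPC by β value (above 0.6; 0.2 to 0.6), and the hypotheses are directional, so other groupings are possible. None of these is adopted as this trial's rule.

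Finally, cut-points and models for an exploratory display may sit in a full protocol or analysis plan that is not shown, and their absence from an article is no error. What remains is that the article does choose a method for this link, and that method requires grouping and yields no estimate. A better use of the same data is available.

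**Conclusion.** The point holds as a minor, low-cost improvement to an exploratory analysis. It is not an error in a primary or secondary analysis. The stated method groups any marker used, leaves the cut open across repeated six-monthly plots, and yields no effect estimate. These statements rest on the text alone.

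The size is conditional. If the curves were tested at a median split, about 64% of the information would be kept. The typical loss would be about 10 to 20 points of power for HR per SD of about 1.5 to 2.5 and 17 to 40 patients, and 1 to 22 points over the wider grid. The hazard ratios, death fractions and test are assumptions. Normality, log-linearity and error-free measurement favour the Cox model. The numbers with a paired sample at Day 57 may be lower than those enrolled.

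**What to change.** In section 2.7, add an explicitly exploratory analysis:

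- Fit one Cox model per primary biomarker, with the change from baseline to Day 57 as a continuous covariate.
- Count survival from the Day 57 sample, because the change is not known before then. State how many patients contribute.
- Report the hazard ratio per SD with its 95% interval, and the number of markers examined.
- Keep the Kaplan-Meier plots as illustration, split at a cut fixed without reference to survival, such as the marker's median.

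The cost is a few sentences and one model per marker on data already collected, with no extra patients, samples or visits. There are two small downsides. Log-linearity is assumed, and a residual plot can check it. Several estimates from a small sample will include some chance findings, which is why the analysis must be labelled exploratory and the number of markers reported.

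### Survival runs from first dose, but sub-groups built on Day 57 marker values are known only eight weeks later, so their Kaplan-Meier curves include eight weeks of guaranteed survival

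*Protocol article*

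**What the plan says.** All references are to the protocol article.

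- **Time zero** (Section 2.7, Data analysis plan): "Overall survival will be calculated as the time from initiation of the trial treatment to death from any cause".
- **Grouping** (Section 2.7): "Kaplan-Meier plots for sub-groups based on primary outcome data will be generated every 6 months for the duration of the study".
- **What the primary outcomes are** (Section 2.1.1): "Determine DNA methylation and XPC levels before, and immediately after treatment, that is, at study entry and after 2 months"; for the immune markers the time points are likewise "immune response in blood before treatment and after 2 cycles".
- **When the samples are taken** (Section 2.3, Data collection): "Before treatment (Day -14) and on Day 57 (week 9) an excision biopsy of subcutaneous metastatic lesion or lymph node", with blood collected at the same two times.
- **How they are analysed** (Section 2.7): "All data for primary outcomes will be tested before and after treatment using paired t-test with Bonferroni correction when required".

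The primary hypothesis at the end of the Introduction is also worded as a change: methylation falls, while XPC and the immune markers rise.

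**The concern.** A patient's before-after change cannot be known until the second sample on Day 57, yet the survival clock for the sub-group plots starts on Day 1. Membership of such a sub-group depends on having survived to Day 57, so the first eight weeks of each curve contain no deaths by construction.

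The cohort has disease resistant to all approved therapies, so some deaths or missing second biopsies before Day 57 are plausible. Two things are at stake. The sub-group curves would show survival that is too favourable in absolute terms, for instance when set beside the whole-cohort curve. And if early deaths were assigned to one of the groups, the plots could suggest that a marker change goes with longer survival when it does not.

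**Working it through.** **Inputs from the protocol.** Clock starts at Day 1 (Section 2.7). Second sample at Day 57 (Section 2.3). Sample size 30 (Section 2.1.2) or 17 + 23 = 40 (Section 2.6); both were run.

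**Assumptions, not in the protocol.** Exponential survival with median m = 4, 6, 9 or 12 months; no true link between marker and survival; two equally likely marker groups; no censoring; two-sided 5% log-rank test. The protocol states no survival figure to reproduce and plans no log-rank test. The test is used here only to measure how far two curves would separate by artefact.

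**Step 1. Guaranteed time.** (57 − 1)/7 = 8.0 weeks, or 56/30.44 = 1.84 months.

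**Step 2. Share dying before Day 57.** 1 − 0.5^(1.84/m) gives 27%, 19%, 13% and 10% for m = 4, 6, 9 and 12 months.

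**Step 3. Only sampled patients are grouped, clock at Day 1.** Under exponential survival the median from Day 1, given survival to Day 57, is m + 1.84: 5.84 against 4.00, 7.84 against 6.00, 10.84 against 9.00, and 13.84 against 12.00. The log-rank statistic depends only on the order of the death times, and the shared 56 days shift every time equally. The test result is therefore the same with the clock at Day 1 or at Day 57. In 6,000 simulated trials per setting the false-positive rate was 5.7-6.6% either way.

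**Step 4. Patients without a Day 57 sample are counted as 'no change', clock at Day 1.** In this simulation the unsampled patients are those who died before Day 57. The true hazard ratio is 1.

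| Assumed median (months) | Die before Day 57 | False-positive rate, n = 30 | False-positive rate, n = 40 | Approximate apparent hazard ratio (n = 30; n = 40) |
|---|---|---|---|---|
| 4 | 27% | 26% | 31% | 0.59; 0.60 |
| 6 | 19% | 16% | 21% | 0.68; 0.68 |
| 9 | 13% | 11% | 13% | 0.76; 0.77 |
| 12 | 10% | 10% | 11% | 0.80; 0.80 |

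**Step 5. After a Day 57 landmark.** The 1.84-month shift disappears because time is counted from Day 57. Early deaths belong to no sub-group, so the false-positive rate is the 5.7-6.6% of Step 3.

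**The case against.** A reader might infer that the plan is likely to produce a spurious survival link. The documents do not support that. The paired t-tests need both samples, so grouping complete pairs is the natural reading, and then the guaranteed time is common to all groups and cancels from the comparison (Step 3). The inflated rates in Step 4 need early deaths to be placed in the 'no change' group, a rule the protocol does not contain, and a log-rank test it does not plan. This part of the objection stands.

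It is also fair to say that 'change' is inferred. Baseline levels are primary outcome data too, and a split on them carries no guaranteed time. But the hypotheses and the paired analyses make change the likelier meaning.

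Overall survival is neither a primary nor a secondary objective, and the plots are exploratory. That limits the weight of the point without removing it.

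Cut-offs and missing-sample rules may properly sit in an analysis plan that is not shown, and their absence is not the finding. The finding is that Section 2.7 already fixes a time zero that does not suit groups formed at Day 57.

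Finally, Section 2.7 says "Overall survival will be calculated at each RECIST data collection point (weeks −1 and 9", and week −1 precedes treatment start. This is loose wording of the assessment schedule. The definition of survival in the same paragraph is clear and no estimate changes, so no weight is put on it.

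**Conclusion.** The point holds in a limited form. If the sub-groups use Day 57 values or changes, their curves from first dose carry 8.0 weeks of guaranteed survival. Under exponential survival the sub-group median is then about 1.8 months too high. Between-group bias does not follow from this alone. It arises only if patients who die before Day 57 are put into one group, in which case the simulated false-positive rate is about 10-26% at n = 30 and 11-31% at n = 40.

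The length of the guaranteed period comes from the protocol. The share of early deaths and the false-positive rates rest on assumed medians of 4 to 12 months and on the other simulation settings. Whole-cohort survival from first dose is unaffected, as are sub-groups defined by baseline values.

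**What to change.** In Section 2.7, state that for any sub-group defined by Day 57 values or by change from baseline, survival starts at a Day 57 landmark and includes only patients alive and sampled then, and that the number who died or had no sample before it is reported. Keep survival from first dose for the whole cohort and for sub-groups defined by baseline values, and say which kind of sub-group is meant.

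The cost is about two sentences and no new data. The drawback is that early deaths leave the sub-group plots, which become smaller and describe survival only beyond Day 57. Those deaths remain in the overall curve.
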